#### Dietary adherence

A 15-item Mediterranean diet adherence survey and a 9-item low-fat diet adherence survey (Appendix 6) will be administered to participants bi-weekly to capture generalised patterns of food consumption during each of the intervention phases. Each survey has been adapted from the PREDIMED study to reflect an Australian food supply and national guidelines for alcohol consumption. While on the Mediterranean diet, participants will also complete a semi-quantitative weekly checklist (Appendix 3, described above). Adherence to the dietary phase will be determined at each bi-weekly visit, where participants must meet a minimum adherence requirement of 75%, as determined by checklists. If participants scoring below 75% are unable to increase their adherence in the next 2 weeks they will be excluded from the study.

To determine the impact of dietary adherence on outcomes an overall Mediterranean diet score [15, 26] will be calculated using data from a 3-day weighed food record (WFR) completed by participants before and at the end of each intervention phase. Further, erythrocyte fatty acids will provide a biological measure of dietary adherence at the end of each intervention phase.

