#### Dietetic counselling

To increase adherence and retention participants will have regular contact with a dietitian. At the beginning of each phase, participants will meet with the dietitian to discuss dietary guidelines in detail. For the Mediterranean diet, participants will be provided with a set of resources, including Mediterranean dietary guidelines (Appendix 1), recommendations on how to include pork in the diet (Appendix 2), education on serving sizes and a Mediterranean diet recipe book. For the continual assessment of adherence, and to encourage familiarity of foods and serving sizes associated with a Mediterranean diet, participants will also be given a semi-quantitative checklist (Appendix 3) to be filled in daily, using a tick system (1 tick = 1 serve), and returned at bi-weekly dietetic visits. While on the low-fat diet, similar dietetic resources will be provided, including a set of low-fat diet guidelines (Appendix 4), education on fat content and a food label reading guide (Appendix 5) to consider when selecting packaged foods.

Throughout each intervention phase participants will attend bi-weekly dietetic visits to discuss their progress, food intake, challenges and any adverse effects. These visits will also include weight measurement to determine body mass, weight loss or weight gain. In the case of weight loss or gain the dietitian will ensure that participants are eating until satiated and discuss mindful eating and portion sizes. If a participant is having trouble adhering to the guidelines the dietitian will discuss strategies and work with the participant to set SMART goals (S, specific; M, measureable; A, achievable; R, realistic; T, time based) for the next 2 weeks.

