The primary analysis will be performed on a per protocol basis including only those subjects who complete both trial phases. A linear mixed effects model will determine the difference in each outcome between dietary interventions and will measure both between and within subject effects for cardiometabolic and cognitive outcomes. If a significant change is detected for cognitive outcomes a hierarchical regression will include cardiometabolic outcomes to assess their meditating effects. A sensitivity analysis will include weight loss, change in physical activity, medications and supplements as these may cause time-varying confounding should they differ between groups in the second dietary phase. Further, carryover and treatment-period effects will be assessed by including treatment*phase and treatment*order interaction terms. A diet*period*energy intake interaction term will be included to determine any significant changes between diets in relation to total energy intake, macronutrient intake and micronutrient intake. As an additional sensitivity analysis we will also include subjects that did not complete the trial or were not included in the per protocol analysis due to inadequate adherence (<75%). For missing data the linear mixed effects models will estimate unbiased effects as opposed to multiple imputation.

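### The 75% adherence rule names no instrument for the low-fat phase, and excluding those who fail it weakens the sensitivity analysis meant to include them

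*Protocol article*

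**What the plan says.** All references are to the protocol article.

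- **Instruments (Dietary adherence).** Two surveys are given bi-weekly: "A 15-item Mediterranean diet adherence survey and a 9-item low-fat diet adherence survey". The next instrument is specific to one diet: "While on the Mediterranean diet, participants will also complete a semi-quantitative weekly checklist".
- **Rule (Dietary adherence).** At each bi-weekly visit, "participants must meet a minimum adherence requirement of 75%, as determined by checklists".
- **Consequence (Dietary adherence).** "If participants scoring below 75% are unable to increase their adherence in the next 2 weeks they will be excluded from the study". Nothing is said about measuring outcomes after that.
- **Low-fat materials (Dietetic counselling).** "While on the low-fat diet, similar dietetic resources will be provided, including a set of low-fat diet guidelines". The other items named are education on fat content and a label-reading guide. No checklist is listed.
- **Primary analysis (Statistical analysis).** "The primary analysis will be performed on a per protocol basis including only those subjects who complete both trial phases".
- **Sensitivity analysis (Statistical analysis).** It adds participants who did not finish and those who "were not included in the per protocol analysis due to inadequate adherence". Missing data are left to the linear mixed model, without multiple imputation.

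**The concern.** There are two linked problems.

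First, the rule is worded for either diet, but the instrument it names is described for one. Applied literally, it can be scored only while a participant is on the Mediterranean diet. The retained sample would then be selected on adherence to one of the two diets being compared.

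Second, the adherence rule ends participation instead of only defining an analysis set. The primary analysis is restricted to those who complete both phases, so the broader sensitivity analysis is the main check on that restriction. Removing people for poor adherence, without further measurement, takes away the data that this check needs. No later analysis plan can recover blood pressure that was never measured.

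**Working it through.** **1. Which instrument serves the rule?** The article uses two words for two kinds of form. The 15-item and 9-item forms are called surveys and exist for both diets. The checklist is the daily tick form returned at dietetic visits (Dietetic counselling), described only for the Mediterranean diet. Dietary adherence says it is completed in addition to the survey, so the two are distinct. The 75% rule cites checklists. It follows that the low-fat phase has a survey but no stated link between that survey and the threshold.

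**2. Which outcomes does an excluded participant have?** Outcome visits are at weeks 0, 8, 16 and 24, and home readings are taken in the week before each (Procedure). I take bi-weekly to mean fortnightly, so dietetic visits fall at weeks 2, 4, 6 and 18, 20, 22. A participant below 75% has two weeks to improve. For exclusion in the Mediterranean phase, with nothing collected afterwards:

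| Order | First below 75% | Re-judged | Outcome weeks available | Both end-of-diet values? |
|---|---|---|---|---|
| Mediterranean first | 2 or 4 | 4 or 6 | 0 | No |
| Mediterranean first | 6 | about 8 | 0, 8 | No |
| Low-fat first | 18 or 20 | 20 or 22 | 0, 8, 16 | No |
| Low-fat first | 22 | about 24 | 0, 8, 16, 24 | Yes |

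Only the last row gives a within-person diet contrast. If the rule also applies in the low-fat phase, the same table holds with the diets exchanged.

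**3. What can the mixed model do with these records?** It can use partial data under missing at random. Here the reason for missingness is poor adherence, which plausibly relates to the response that would have been seen. The observed blood pressures need not account for that.

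**4. How much could it matter?** The article gives no expected exclusion rate and no relation between adherence and response. The following is therefore illustration only.

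- *Implied SD of the paired difference*, taking the stated 90% power, N = 31 and 2.5 mmHg at face value (two-sided 5%, normal approximation): 2.5 × √31 / (1.960 + 1.282) = 4.29 mmHg. The article's last sample-size step reproduces: 124 × (1 − 0.5)/2 = 31. I do not rely on how the 124 was reached.
- *Shift in the completer estimate* if the least adherent fraction p is removed and adherence has correlation c with the paired difference: c × 4.29 × φ(z_p)/(1 − p), where φ is the normal density and z_p the p-quantile.
  - p = 0.1, c = 0.1: 0.1 × 4.29 × 0.195 = 0.08 mmHg.
  - p = 0.2, c = 0.3: 0.3 × 4.29 × 0.350 = 0.45 mmHg.
  - p = 0.3, c = 0.5: 0.5 × 4.29 × 0.497 = 1.07 mmHg.
- *Power of the completer analysis*, Φ(2.5√n/4.29 − 1.960): 86.9% with 28 completers, 82.9% with 25 and 78.0% with 22. The target in Table 1 is 31, the same number the power calculation requires.

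Against a 2.5 mmHg target, the shift runs from negligible to material, depending wholly on assumed inputs. The formula gives a magnitude; its sign is that of c, which the article does not inform.

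**The case against.** The strongest reply is that the authors probably meant the rule to cover both diets. It speaks of the dietary phase in general, uses checklists in the plural and refers to scoring, which fits a 9-item survey. The list of low-fat resources is introduced as examples, and the appendices holding the forms are not shown. This stands in part: a reader might infer that exclusion can happen only on the Mediterranean diet, and the document does not establish that. It establishes only that the low-fat instrument is not named. The loss of outcomes after exclusion remains under either reading.

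A reader might also infer that the sensitivity analysis is impossible. It is not. Late failures may reach the end-of-phase assessment, those excluded in their second phase keep three time points, and the model accepts partial records. Listing the low-adherence group separately from non-completers even suggests that some were expected to have data, so exclusion may partly mean exclusion from the per protocol set. The text under Dietary adherence says otherwise, and the two sections need reconciling.

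Finally, a reader might infer a definite bias towards the Mediterranean diet because poor low-fat adherers stay in and dilute that diet's effect. In a cross-over, an excluded person leaves both sides of the comparison, and low-fat non-adherers would remain even with complete follow-up. Dilution therefore does not measure what exclusion does. If adherence is correlated across diets, removing poor Mediterranean adherers also raises low-fat adherence, which offsets some of any asymmetry.

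**Conclusion.** The point holds in a limited form. As written, the 75% rule has no named instrument in the low-fat phase, so it may select on Mediterranean adherence only. Participants excluded before the end of a phase lack that phase's final blood pressure and usually any within-person contrast. The promised sensitivity analysis would therefore be a weak check on a per protocol primary analysis and would lean on a missing-at-random assumption that is hard to defend here.

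Neither the size nor the direction of a bias can be derived from the document. The 0.08 to 1.07 mmHg range rests on assumed exclusion of 10 to 30% and assumed correlations of 0.1 to 0.5, and is not an estimate for this trial. The conclusion also assumes that no outcomes are collected after exclusion, which the article neither states nor rules out. This is a cheap improvement to the plan, not a demonstration that its result would be wrong.

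**What to change.** - Name the adherence measure for each phase. The 15-item Mediterranean and 9-item low-fat surveys are already collected bi-weekly and can carry the 75% threshold in both.
- Use that threshold only to define the per protocol analysis set.
- State that the scheduled week 8, 16 and 24 outcomes are collected from all randomised participants regardless of adherence.
- Reconcile the wording under Dietary adherence, where non-adherers leave the study, with the sensitivity analysis under Statistical analysis, which includes them. Whether a non-adherer continues the diet stays with the investigators.

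The cost is a change of wording and a few assessment visits that are already in the schedule. The change does not enlarge the per protocol set; it gives the wider analysis real outcomes to work with. Table 1 lists recruitment as complete, so it may come too late for participants already excluded. For any such participants, the report should give their number, the diet and week of exclusion, and the outcomes available.

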#### Mediterranean diet

Guidelines for the Mediterranean diet are adapted from Estruch et al. (2013) for an Australian food supply:Minimum of one tablespoon (20 mL) of EVOO per day;≥2–3 daily servings of fresh fruit (one serve = 150 g fresh, 30 g dried, or one cup canned in natural juice);≥3 weekly servings of legumes (one serve = 75 g);2-3 weekly servings of fresh, lean pork (one serve = 100 g cooked)≥3 weekly servings of fish and seafood (at least one serving of oily fish) (one serve = 100 g cooked);≥5 weekly serving of raw or roasted nuts or seeds, without added salt, sugar or chocolate (one serve = 30 g; 7.5 g hazelnuts, 15 g walnuts, 7.5 g almonds supplied for each serve);Ad-libitum consumption of wholegrain cereal products (bread, pasta, rice, cereal) and dairyAd-libitum consumption of eggs, not to exceed 6 serves per week (1 serve = approx. 70 g or 1 egg)Select white meats (poultry without skin) instead of red meats or processed meats;Limit consumption of red and cured meat (remove all visible fat) to ≤1 serve/week (one serve of red meat/cured ham = 100 g);Limit consumption of chocolate to ≤1 serve/week (one serve of chocolate = 50 g);Use EVOO for cooking and dressing vegetables and salad;Cook regularly (at least twice a week) with a tomato based sauce (EVOO, tomato, garlic and onion);Dress vegetables, pasta, rice and other dishes with EVOO, tomato, garlic and onion sauce;Eliminate or limit the consumption of cream, butter, margarine, cold meat, pate, duck, carbonated and or sugared beverages, pastries, commercial bakery products (cakes, donuts, cookies), desserts (puddings), French fries, potato crisps, sweets;For usual drinkers, red wine is recommended as the main source of alcohol with a maximum of two standard drinks per day (200 mL = two standard drinks) [46]

Participants will be advised to consume pork in place of chicken and red meat ensure that total meat consumption does not exceed 400 g per week.

To assist with adherence, the following foods will be provided each week: 375 ml EVOO; 250 g of fresh, lean pork; 150 g raw, unsalted almonds, walnuts and hazelnuts; 225 g (net weight) of canned chickpeas, red kidney beans, 4-bean mix and lentils; 95 g of canned tuna and 95 g of canned salmon.

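### The adherence score meant to explain outcomes uses 3-day food records, although most defining foods are set per week; add a whole-phase checklist score within the Mediterranean phase

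*Protocol article*

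**What the plan says.** The Protocol article, Dietary adherence, gives the purpose of the score ("To determine the impact of dietary adherence on outcomes") and its source: "an overall Mediterranean diet score [15, 26] will be calculated using data from a 3-day weighed food record (WFR"). The record is "completed by participants before and at the end of each intervention phase". Under Procedure, home measures, including this record, are collected in the week before each of the four assessment visits. One 3-day window therefore stands for the end of an 8-week phase.

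Under Mediterranean diet, the main foods carry weekly targets or limits:
- legumes: "≥3 weekly servings of legumes (one serve = 75 g")
- pork: "2-3 weekly servings of fresh, lean pork (one serve = 100 g cooked")
- fish: "≥3 weekly servings of fish and seafood (at least one serving of oily fish")
- red and cured meat: "Limit consumption of red and cured meat (remove all visible fat) to ≤1 serve/week"

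Nuts (at least 5), eggs (at most 6), chocolate (at most 1) and tomato-based sauce (at least 2) are also weekly. Of the 11 items with a stated frequency or limit, 8 are weekly. The three daily ones are olive oil, fruit, and wine for usual drinkers.

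Two other instruments run through the Mediterranean phase. One is a serve checklist (Dietetic counselling) "to be filled in daily, using a tick system (1 tick = 1 serve), and returned at bi-weekly dietetic visits"; the other is a 15-item survey given bi-weekly. The checklist determines the 75% adherence requirement. Neither is named as a source for the score that is to be related to outcomes.

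**The concern.** A food eaten one to five times a week cannot be placed accurately from three days. The count depends heavily on which days were recorded. For an explanatory variable this is measurement error: it adds spread unrelated to true adherence and pulls a fitted adherence-outcome slope toward zero. With a target of 31 participants there is little precision to spare. A flat slope could mean that adherence has no bearing on blood pressure or cognition, or only that the score ordered participants poorly, and the 3-day score alone could not separate the two.

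**Working it through.** The article states no figure for the precision of the score, so there is none to reproduce. The check takes its frequencies from the Mediterranean diet section and the three-day window from Dietary adherence.

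**Model.** A food is eaten on m days of a 7-day week, one serve per eating day, and 3 of the 7 days are recorded. The number k of eating days in the record is hypergeometric: P(k) = C(m,k)·C(7−m,3−k)/C(7,3), with C(7,3) = 35. The weekly estimate is k × 7/3.

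**Fish at 3 days a week.** P(k = 0, 1, 2, 3) = 4/35, 18/35, 12/35, 1/35 = 11.4%, 51.4%, 34.3%, 2.9%. The corresponding estimates are 0, 2.33, 4.67 and 7 serves/week. The mean is (18 + 24 + 3)/35 × 7/3 = 3, so the estimate is unbiased but coarse.

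**Absence of other foods from the record.**
- Legumes at 3 a week: 4/35 = 11.4%.
- Pork at 2 a week: 10/35 = 28.6%; at 3 a week, 11.4%.
- Oily fish at 1 a week: 20/35 = 57.1%.

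**Sampling variance of the weekly estimate.** Var(k) = 3·(m/7)·(1 − m/7)·(4/6) = 2m(7−m)/49. Multiplying by (7/3)² gives (2/9)·m(7−m). At m = 3 this is (2/9) × 12 = 2.67, so SD = 1.63. This is the maximum over whole m (reached at 3 and 4); the variance is 2.22 at m = 2 or 5 and 1.33 at m = 1 or 6.

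**Reliability of the fish component.** Let true intake have mean 3 and between-person SD s (assumption). Because the variance depends on m, it is averaged over participants: (2/9)·(7×3 − 9 − s²) = (2/9)·(12 − s²). Reliability is s² divided by s² plus this average.

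| s (assumed) | mean error variance | reliability | slope lost |
|---|---|---|---|
| 1 | (2/9)×11 = 2.44 | 1/3.44 = 0.29 | 71% |
| 1.5 | (2/9)×9.75 = 2.17 | 2.25/4.42 = 0.51 | 49% |
| 2 | (2/9)×8 = 1.78 | 4/5.78 = 0.69 | 31% |

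**From one component to the whole score.** An illustrative simulation combined four weekly foods with two well-measured daily items, under assumed between-person spreads. The slope on the observed score was 0.45 to 0.89 of that on the true score within the Mediterranean phase. A second simulation, of the four weekly foods pooled over both phases, gave about 0.86. Days were drawn independently, which makes the error variance 1.5 times the hypergeometric one. These figures show only that the composite may be diluted less than a single food.

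**Sensitivity to the pattern of days.** If fish is eaten on Monday, Wednesday and Friday and three consecutive days are recorded, the seven possible starts give counts of 2, 1, 2, 1, 1, 1, 1. Fish is then never absent. Var(k) = 13/7 − 81/49 = 10/49, so the SD of the estimate is √(10/49 × 49/9) = 1.05 serves/week. Evenly spaced eating reduces the noise but does not remove it.

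**The case against.** The strongest defence is that the weighed record is the sensible common instrument. It is taken before and after each diet, so it supports change scores and between-diet comparison in a cross-over. The checklist exists only on the Mediterranean diet. Replacing the weekly components with ticks in one phase would confound instrument with diet. This stands, and it rules out substitution.

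A reader might also infer that fully adherent participants will often be mis-scored. Applying the article's dietary targets to the scaled record would put a participant at exactly 3 fish serves below target in 22/35 = 63% of records. The documents do not support that as a statement about the score. The targets are dietary advice and are not stated to be the scoring key, and the cited score's components and cut-offs are not reproduced. If the score is continuous, the fault is random noise rather than misclassification. The figure also assumes intake exactly at the minimum: at 4 fish days a week it falls to 37%, and at 5 to 14%.

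The article also plans erythrocyte fatty acids as a biological adherence measure. That is a real second source, but Secondary outcome measures and covariates makes the assay conditional on further funding.

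Finally, weighed days against unweighed ticks is a trade-off, and an article may leave the adherence model to fuller documents. Both points are fair and keep this a modest matter. The source of the score, however, is stated in the article itself.

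**Conclusion.** The concern holds as a measurement-error problem confined to the adherence-outcome analysis. The weekly components carry large day-sampling noise: an SD of 1.63 serves/week for fish at 3 days a week, and reliability of about 0.29 to 0.69 for that component under the assumed spreads. These figures rest on one serve per eating day, three of seven days sampled without regard to eating pattern, and the same eating frequency every week. The 75% rule may narrow true differences in adherence, which would push reliability toward the lower end. Dilution of the overall score should be smaller, and its size cannot be fixed from the article.

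A reader might go further and conclude that the trial's main result, or the 75% rule, is compromised. Neither follows: the primary blood pressure comparison does not use this score, and the 75% rule uses checklists. Nor is a null adherence result assured; the point is only that such a result from the 3-day score alone would be hard to interpret. This is an inexpensive improvement, not a fundamental flaw.

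**What to change.** Keep the 3-day weighed-record score for before/after and between-diet comparisons, and keep the record for foods eaten daily and for energy and nutrients.

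For the adherence-outcome analysis within the Mediterranean phase, also pre-specify a second score. Take its weekly foods (fish, legumes, nuts, pork, red and cured meat) from the daily serve checklist averaged over the 8 weeks, and use the bi-weekly 15-item survey for any food the checklist does not list. Report results with both scores, and state that a null result from the 3-day score alone will not be read as evidence that adherence does not matter.

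The cost is analysis wording only, since the checklist and survey are already collected. The limits should be stated: ticks are unweighed self-report, the checklist covers only the Mediterranean phase, and the 75% rule narrows its range among those retained.
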